## Abstract

This paper describes a currently on-going multicenter, randomized controlled trial designed to assess the efficacy of calf neuromuscular electrical stimulation (NMES) on changes in maximal walking distance in people with lower extremity peripheral artery disease (PAD), compared with a non-intervention control-group. This study (NCT03795103) encompasses five participating centers in France. PAD participants with a predominant claudication at the calf level and a maximal treadmill walking distance ≤300 m are randomized into one of the two groups: NMES group or Control group. The NMES program consists of a 12-week program of electrical stimulations at the calf-muscle level. The primary outcome of the study is the change in maximal treadmill walking distance at 12 weeks. Main secondary outcomes include changes in the pain-free treadmill walking distance; 6 min total walking distance; global positioning system (GPS)-measured outdoor walking capacity; daily physical activity level by accelerometry; self-reported walking impairment; self-reported quality of life; ankle-brachial index; and skin microvascular function, both at the forearm and calf levels. Recruitment started in September 2019 and data collection is expected to end in November 2022.

## 1. Introduction

Lower extremity peripheral artery disease (PAD) is a serious public health concern with an estimated prevalence in people aged 25 years and older of 5.5% worldwide (236.62 million people), 7.99% in the European Region (51.1 million people) and 9.79% in France (4.42 million people) [1]. PAD is associated with an increased risk of disability and mortality as compared to people without PAD [2]. Atherosclerosis is the main cause of PAD and causes the chronic narrowing of arteries that induces lower limb blood-flow impairment [3,4]. This hemodynamic impairment can induce ischemic pain which severely impairs the performance of daily physical activities such as walking [5], which progressively becomes very disabling and isolates people living with PAD [6].

Current care for PAD patients includes lifestyle modification (i.e., cessation of smoking and dietary habit modifications) and medical therapy to lower the cardiovascular risk [7]. In addition, before considering a possible revascularization procedure (surgical or endovascular), supervised or home-base exercise should be proposed as the first-line therapy to decrease leg symptoms and improve walking capacity [3,8]. Compared to medical treatment alone, interventions such as supervised exercise have resulted in enhancements in walking capacity [8] due to an improvement in endothelial vasodilator function or skeletal-muscle adaptations [9]. However, there is a lack of easy access to structured exercise therapy due to several barriers resulting in this efficacious therapy remaining largely unavailable to the majority of patients [10]. Furthermore, PAD patients with walking pain symptoms are often unable or reluctant to partake in exercise [10,11].

Given the need for additional therapy strategies, additional methods such as neuromuscular electrical stimulation (NMES) have been proposed [12,13,14]. Interestingly, Abraham et al. [15] showed that NMES of calf muscles results in a significant increase of arterial inflow without measurable muscle ischemia or pain. Several vascular and/or nonvascular pathways have been proposed to support the potential efficacy of NMES on the improvement of walking performance in people with PAD [13]. However, a recent systematic review concluded that it was not yet possible to draw a conclusion on the potential efficacy of NMES on walking performance in people with PAD because of the very low number of available studies with adequate sample size and low risk of bias [13]. Moreover, the two available randomized controlled trials (RCTs) testing home-based NMES programs alone to improve walking performance included short-duration NMES programs (1 month) [12,14]. Maximal walking distance (MWD) was increased in these two studies (by 39 m to 40 m, or 34% to 35%). However, it is likely that a longer duration intervention of 3 months, a more usual duration in exercise-therapy interventions, would have induced larger improvements in walking performance.

The primary objective of the ELECTRO-PAD study is to assess the efficacy of NMES on changes in MWD after a home-based 12-week program in people with PAD by comparing two groups: (1) an intervention group receiving the NMES program, and (2) a non-intervention control group with no intervention. Both groups receive standard care including usual medical treatment and usual non-structured walking incitation to walk on their own daily.

## 2. Materials and Methods

### 2.1. Study Design

The ELECTRO-PAD study is a prospective, randomized, multicenter, single-blind (investigator-blinded), superiority clinical trial with two parallel groups and a primary endpoint of MWD change at 12 weeks following an NMES program. Recruitment for the study commenced in September 2019 and the study end is planned for November 2022.

The study protocol is reported here in accordance with the SPIRIT 2013 recommendations for reporting standard protocol items for Clinical Trials [16]. Information required for those recommendations which could not be directly reported in the manuscript are presented in File S1. Figure 1 shows the schedule of pre-screening, enrolment, interventions, and assessments for the ELECTRO-PAD study. The protocol was reviewed and approved by the sponsor and the applicable French institutional ethical committee (CPP: “*Comité de Protection des Personnes*”) with respect to scientific content and compliance with applicable research and human subjects’ regulations, according to the French law and the Declaration of Helsinki (CPP reference 2018/07). The ELECTRO-PAD study was registered on ClinicalTrials.gov (NCT03795103). A Clinical Research Officer mandated by the promoter ensured participant safety and good practices of the clinical study. The coordinating center was certified to conduct such randomized controlled trial.

In parallel to this clinical trial, two ancillary studies were performed. The first ancillary study was performed only in PAD participants included in the Rennes coordinating center due to material availability. The aim of this ancillary study was to assess the skin microvascular function in the included participants both at visits #1 and #2, between 1 and 14 days after the corresponding visit (Figure 1). A second ancillary study was also performed, but on a distinct group of healthy participants with no intervention. The main aim of this second ancillary study was to determine the normal range for most of the different outcome measures that were performed in PAD participants. In that way, procedures performed by this group of healthy participants were almost the same as those performed by the participants with PAD. Inclusion and Exclusion criteria for healthy participants are reported in File S1 (item 2b).

### 2.2. Recruitment, Randomization, and Blinding

Participants are being identified and recruited by the investigators from five French university hospitals located in the northwest (n = 4) and the southwest (n = 1) of France: Rennes (coordinating center), Angers, Brest, Caen, and Toulouse. In each center, participants are screened for eligibility during their usual medical appointment for PAD management, and during which a modified Strandness treadmill walking test (3.2 km/h, 10%) was performed to assess walking ability (see outcomes assessment). Eligible participants who meet the inclusion criteria (Table 1) were asked to participate in the study. A letter presenting the objectives and the protocol sequence is given to the participant (File S2) and, after ≥ a 48-h period, the participant is called by phone by a member of the local staff. If the participant agrees to participate, the inclusion visit (visit #1) is planned, preferably within the next 7 to 21 days (Figure 1). This strategy for participant enrolment is designed to: (i) minimize the burden of planning numerous inclusion visits (visit #1) while the potentially eligible participants had in fact a MWD > 300 m (exclusion criteria); and (ii) test the reproducibility of the treadmill walking test by assessing the variability of the MWD [17]. No inclusion percentage to achieve was given to each center. The enrollment period is anticipated to last ~43 months from study commencement (including enrollment of healthy participants in the second ancillary study).

Inclusion and exclusion criteria for participants with PAD are displayed in Table 1. In addition, criteria for discontinuing allocated interventions are presented in File S1 (Item 11b). Participants provide paper-based written, informed consent before they participate in the study (File S2), which is collected by the assessor at visit #1 (inclusion visit, Figure 1). At visit #1, the order of the treadmill test and 6 min test is first randomized electronically, and the information is given to the assessor of the local center where the participant performs both tests accordingly. Once visit #1 is achieved, following an electronic process (File S1, Item 16a), each participant is randomized into one of the two arms (1:1) of the study: (1) NMES group; or (2) Control group (CONT). Randomization is performed as block randomization with a 1:1 allocation. The randomization is stratified and equilibrated (block for equilibration not provided here to preserve concealment allocation) in the five inclusion centers. Only the biostatistician, the data manager, and the research associate at the coordinating center have access to the allocation sequence to preserve the allocation concealment. In that way, the assessor of the different outcomes in each center is blinded to the participant treatment group allocation. The research associate of the coordinating center receives an email mentioning the participant group allocation. Then the research associate mails a box containing the following to the participant’s home:for both groups of participants: (i) a box containing the monitors for daily physical activity (PA) and outdoor walking-capacity assessment; (ii) a handbook that explains how to wear the monitors, how to perform the outdoor walking sessions, and that includes a diary to report different information (see below and File S3); (iii) a sealed envelope containing a brochure with advice for regular PA on a day-to-day basis (File S4).for the NMES group only: (i) an opaque box containing the NMES device; (ii) a sealed envelope containing the NMES handbook for implementation and follow-up of the NMES program (Files S5 and S6).

At the coordinating center, the box is directly hand-delivered to the participant. The research associate calls on each participant once the box is received at their home (identified via a parcel-tracking system). In that way, the research associate indicates the appropriate box to open first and that contains PA monitors. The research associate then explains how to install and wear the monitors verbally while the participants read the guidebook that contains all the information needed. A second call phone is scheduled at the end of the 7-day free-living PA-measurement period during which the research associate discloses the group allocation to the participant.

Due to the nature of the intervention and the follow-up, the participants and the research associate cannot be blinded to allocation, but participants are strongly encouraged not to disclose their allocation status during visit #2. Due to personnel availability at the coordinating center, the assessor of skin microvascular function assessment at both visits (ancillary study #1), and the 6 min walking tests at visit #2 is not blinded to the participant’s treatment arm.

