### 2.8. Data Collection, Management, and Analysis

*Data collection and management.* The data collected are in an electronic Case Report Form (eCRF) and data monitoring is carried out on a regular basis (~every six months).

*Statistical analysis (see also File S1, item 20a).* Descriptive statistics will be performed to describe the baseline characteristics of interest at the level of the two groups and for the different outcomes. Continuous data will be expressed as mean +/− standard deviation or median values with interquartile range, depending on the distribution. A normality test will be carried out to judge the Gaussian or non-Gaussian distribution of the data of the continuous variables studied. Two-sample, two-sided t-tests (or Mann–Whitney U test) and χ2 tests will be used to compare continuous and categorical characteristics of participants across the two groups at baseline, respectively.

For statistical analysis of the primary and secondary outcomes after study completion, two -sample, two-sided t-tests (or Mann–Whitney U test if the data is not normally distributed) will be used to compare changes in outcomes between baseline and the 3-month follow-up between the NMES and the CONT groups. However, in case of imbalance in baseline characteristics between the 2 groups, outcome data will be analyzed using linear regression models adjusting for significantly different baseline data between the two groups [46].

Firstly, an intention-to-treat analysis will be performed. As recommended [47], a missing at random (MAR) assumption will be made for missing data for principal analysis by performing complete cases and multiple imputation analysis. Deviation from MAR will also be assessed with sensitivity analysis under the missing not at random (MNAR) assumption, using controlled multiple imputation with different controlled scenarios. A per-protocol analysis will be also performed considering only participants with data available both at visit #1 and visit #2.

A subgroup analysis will be performed to explore the potential association between change in treadmill MWD and reported walking activity changes during the follow-up. In the NMES group, potential association between the total dose of NMES over the program and change in treadmill MWD will be assessed.

Statistical analysis will be carried out using R software [48]. The level of significance will be fixed at *p* < 0.05.

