**Inclusion Criteria**
Age > 40 years old. Subjects with Lower Extremity Peripheral Artery disease (LEPAD). LEPAD is defined by the presence of at least one of the following criteria: History of revascularization in the lower limbs due to LEPAD OR Ankle brachial index (ABI) of ≤0.90 ^1^ OR ABI or ankle systolic blood pressure decrease during recovery from treadmill walking test >20% or >30 mmHg, respectively OR Toe-brachial index ≤ 0.70 if ABI cannot be measured and if incompressible arteries are suspected Complain of exertional calf pain (fatigue, discomfort or cramping) that can begin or not at rest, causes the participant to stop walking and relieves or lessens within 10 min of rest (assessed using the San Diego questionnaire AND confirmed during treadmill testing). Pain (fatigue, discomfort, or cramping) that is mainly located at the calf level. Maximal walking distance on treadmill < 300 m (treadmill protocol: 3.2 km/h, 10% grade). Subject receiving for at least one month the recommended medical therapy for LEPAD management (antiplatelet therapy and statin medication). Obtained informed consent.

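### The primary analysis is an unadjusted test on change from one baseline; adjusting for the two treadmill tests already done before randomisation would be more precise

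*Protocol article*

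**What the plan says.** All references are to the protocol article.

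- **Screening test (section 2.2).** Candidates are seen at a usual appointment, "during which a modified Strandness treadmill walking test (3.2 km/h, 10%) was performed to assess walking ability". The inclusion visit follows a phone call: "the inclusion visit (visit #1) is planned, preferably within the next 7 to 21 days".
- **Visit #1 test (section 2.2).** The treadmill test is done again: "At visit #1, the order of the treadmill test and 6 min test is first randomized electronically".
- **Allocation (section 2.2).** The arm is assigned only once visit #1 is complete, so both treadmill tests precede randomisation.
- **Purpose of the repeat (section 2.2).** Two purposes are given. One is to avoid booking inclusion visits for people who walk too far to qualify. The other is to "test the reproducibility of the treadmill walking test by assessing the variability of the MWD".
- **Primary analysis (section 2.8).** Two-sample, two-sided t-tests, or Mann–Whitney tests if the data are not normal, "will be used to compare changes in outcomes between baseline and the 3-month follow-up between the NMES and the CONT groups". Linear regression is reserved for the case of baseline imbalance, and then adjusts for the characteristics that differ significantly.
- **Which test is the baseline.** Section 2.8 does not name the visit. The heading of section 2.6 lists visits #1 and #2 for outcome assessment, so visit #1 is the implied baseline.

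**The concern.** A change score subtracts the whole of the baseline value, including its day-to-day measurement noise. A model of the 12-week value adjusted for baseline subtracts only the part that predicts follow-up, so its residual variance is never larger under equal variances. A second pre-randomisation reading of the same quantity improves the prediction further. The plan makes no use of the second reading and makes adjustment conditional on an observed imbalance.

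This matters because the trial is small. Section 2.7 needs about 29 per group and enrols 40. At the planned maximum dropout of about 30%, 40 × 0.70 = 28 per group remain, one below that minimum. Precision that costs no recruitment is useful there.

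**Working it through.** **1. The plan's own figure.** Inputs from section 2.7: difference 58 m, SD 78 m, alpha 0.05 (two-sided, from section 2.8), power 80%.

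n per group = 2 × (1.960 + 0.842)² × (78/58)² = 28.4, rounded up to 29. The stated 29 reproduces by the normal approximation; the t-based value is 29.4, so 30. The sample size does not depend on a second baseline.

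**2. Assumed inputs.** The article gives no correlations. Let b be the correlation between the screening and visit #1 tests, taken as 0.80 to 0.90. Let r be the correlation of either test with the 12-week value, taken as 0.6 to 0.8. Variances are assumed equal on all three occasions and set to 1.

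**3. Formulas for the variance behind the between-arm contrast.**

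- Change from visit #1 (planned): 2(1 − r)
- Linear model adjusted for visit #1: 1 − r²
- Linear model adjusted for both tests: 1 − 2r²/(1 + b)

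Under these equal-variance, equal-correlation assumptions, two separate covariates give the same residual variance as their mean. Separate entry also lets the weights differ if the assumptions fail.

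**4. Midpoint, b = 0.85 and r = 0.7.**

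- Change score: 2 × 0.3 = 0.600
- Adjusted for visit #1: 1 − 0.49 = 0.510, a cut of 15%
- Adjusted for both: 1 − 0.98/1.85 = 0.470, a cut of 22%
- Share due to the second test: 1 − 0.470/0.510 = 8% of the adjusted residual variance

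**5. Range.**

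| r | b | Change score | Adjusted, visit #1 (cut) | Adjusted, both (cut) | Second test, of adjusted residual variance |
|---|---|---|---|---|---|
| 0.6 | 0.80 | 0.800 | 0.640 (20%) | 0.600 (25%) | 6% |
| 0.6 | 0.90 | 0.800 | 0.640 (20%) | 0.621 (22%) | 3% |
| 0.7 | 0.80 | 0.600 | 0.510 (15%) | 0.456 (24%) | 11% |
| 0.7 | 0.90 | 0.600 | 0.510 (15%) | 0.484 (19%) | 5% |
| 0.8 | 0.80 | 0.400 | 0.360 (10%) | 0.289 (28%) | 20% |
| 0.8 | 0.90 | 0.400 | 0.360 (10%) | 0.326 (18%) | 9% |

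The 28% and 20% figures need the 12-week correlation to be as high as the short-interval one.

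**6. What it means for power (t-based, difference 58 m, midpoint correlations).**

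- *If 78 m is the SD of change*: at 28 per group, power is 78% for the planned test, 84% adjusting for visit #1 and 87% adjusting for both. At 40 per group the planned test already has 91%.
- *If 78 m is the SD of MWD itself*: the SD of change is 78 × √0.6 = 60.4 m, and power at 28 per group is already 94%. It rises to 97% and 98%. The gain is then mainly a narrower confidence interval.

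These figures describe the t-test and linear model, not the Mann–Whitney branch.

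**The case against.** The strongest reply is that nothing here is wrong. Change from visit #1, compared between randomised arms, is unbiased, and the stated sample size stands without a second baseline. Visit #1 is the protocol-run test with a matching visit #2, whereas the screening test belongs to a routine appointment before consent. The screening value is truncated by the 300 m limit and may carry a familiarisation effect. The full protocol, File S1 or an analysis plan may define the baseline and covariates more closely. Most of this stands. It makes the point an efficiency improvement, and it argues for separate covariates over a simple average. It does not remove the point, because section 2.8 does commit to an unadjusted comparison with adjustment conditional on imbalance.

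A reader might also infer more than the article supports:

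- **That the 300 m limit costs precision.** Table 1 ("Maximal walking distance on treadmill < 300 m") does not name the test occasion. That bears on who is enrolled, not on the variance of the comparison.
- **That selection on MWD distorts the result through regression to the mean.** Any such drift is equal in both arms by randomisation. Averaging in the screening test would not reduce it. Take an assumed referral population with mean 200 m and SD 120 m, selected at screening below 300 m. The screening mean falls 42.4 m below 200. At b = 0.85 and r = 0.7, visit #1 lies 36.0 m below and follow-up 29.7 m below. The spurious rise is about 6.4 m from visit #1 but 39.2 − 29.7 = 9.5 m from the two-test mean.
- **That the paired tests serve reproducibility alone.** Section 2.2 also uses the first test to avoid needless inclusion visits.

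**Conclusion.** The point holds as a minor, optional gain in precision. The planned analysis is valid but less efficient than the data already collected allow. Under the assumed correlations, the model with both tests has 18 to 28% less variance than the planned change score (22% at the midpoint). At the midpoint, 15 of those 22 points come from adjusting for visit #1 at all; the second test is the smaller part. The practical value is greatest if 78 m is the SD of change and dropout nears its planned maximum, and small otherwise. Confidence in the exact size is low, because the article gives neither correlation and the equal-variance assumption is untested.

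**What to change.** Before unblinding:

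1. Name visit #1 as the baseline, and keep it for descriptive change.
2. Make the primary analysis a linear model of 12-week MWD with treatment and visit #1 MWD as covariate, fitted whatever baseline imbalance is observed.
3. Add screening MWD as a second, separate covariate. Where it is missing, use visit #1 alone, by a rule stated in advance.

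The cost is a revised analysis paragraph and one extra covariate. The screening values are needed anyway for the stated reproducibility assessment, so no patients, visits or procedures are added. If only one change is made, it should be step 2, which brings most of the gain at the midpoint.

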## Figures and Tables

**Figure 1 jcm-11-07261-f001:**
[figure not shown]
Flowchart for participant screening for eligibility, inclusion, assessments, randomization, interventions, and follow-up. ***Legend.*** WIQ: Walking Impairment Questionnaire; PAQ: Peripheral Artery Questionnaire; FFQ: Food Frequency Questionnaire; TcPO_2_: Transcutaneous oxygen pressure measurement; PA: Physical Activity; GPS: Global Positioning System; NMES: Neuromuscular Electrical Stimulation. Note that participants’ allocation to NNMS or CONTROL groups following randomization is concealed to the participants until they complete the 7-day physical activity measurement.

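### Baseline physical activity, walking-pain and GPS data are collected after randomisation while only the NMES arm holds an extra box and envelope, so the stated concealment from participants in that week cannot be relied on

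*Protocol article*

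**What the plan says.** All references are to the protocol article.

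- **Randomisation (section 2.2).** "Once visit #1 is achieved, following an electronic process (File S1, Item 16a), each participant is randomized into one of the two arms". Next, "The research associate of the coordinating center receives an email mentioning the participant group allocation", and that person then sends out the material.
- **Both arms receive (section 2.2)** "a box containing the monitors for daily physical activity (PA) and outdoor walking-capacity assessment", a monitor handbook with diary, and one sealed envelope with the activity brochure.
- **One arm receives more (section 2.2).** The list continues "for the NMES group only: (i) an opaque box containing the NMES device" and "a sealed envelope containing the NMES handbook for implementation and follow-up of the NMES program". No matching dummy item for controls is described.
- **Set-up (section 2.2).** Once the parcel has arrived, a phone call follows in which "the research associate indicates the appropriate box to open first and that contains PA monitors". Allocation is disclosed in a second call, when the 7 days are over. For the coordinating center: "At the coordinating center, the box is directly hand-delivered to the participant".
- **Concealment (Figure 1 legend).** Allocation "is concealed to the participants until they complete the 7-day physical activity measurement".
- **Use of the data (sections 2.5, 2.6.2 and 2.8).** Daily activity (including walking pain) and GPS outdoor walking capacity are secondary outcomes. Both are recorded in the 7-day week after each visit, and the arms are compared on change from baseline to 3 months.

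**The concern.** A baseline is safe to subtract or adjust for when allocation cannot have influenced it. That is guaranteed if it is recorded before randomisation. If it is recorded afterwards, it depends on participants not knowing their arm. Here the second condition has to carry the weight, and the delivery arrangements weaken it. A participant who expects that one arm is given a device can count the items in the parcel before the week begins.

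The outcomes at stake depend on behaviour: free-living steps, self-timed outdoor walks, and a button pressed when pain occurs. Someone who guesses their arm may walk more, walk less or report pain differently. The baseline would then contain an effect of allocation, and the change from baseline would no longer estimate the effect of NMES cleanly.

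**Working it through.** **1. Order of events (sections 2.2, 2.6.2 and 2.8)**

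| Step | Event | Does the parcel reveal a difference by then? |
|---|---|---|
| 1 | Visit #1: treadmill test and 6 min test | No, not yet randomised |
| 2 | Randomisation; research associate informed | Not to the participant |
| 3 | Parcel delivered or handed over | Yes: one box more and one envelope more in the NMES arm |
| 4 | Set-up call by the research associate, who knows the arm | Yes |
| 5 | 7-day activity, pain and GPS measurement | Yes |
| 6 | Second call: planned disclosure | Arm told |

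The legend places the end of concealment at step 6. The itemised contents put a visible difference at step 3.

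**2. Contents by arm.** Control: one inner box (monitors), one handbook, one sealed envelope. NMES: the same, plus one opaque box and one further sealed envelope. Opacity and sealing protect the contents, not the count.

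**3. The plan's own figure.** The only sample size given is for the primary outcome (section 2.7): a difference of 58 m, SD 78 m, two-sided alpha 0.05 and 80% power. n = 2 × (1.960 + 0.842)² × 78² / 58² = 28.4, so 29 per arm, as stated. This point does not touch that figure.

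**4. How a baseline shift enters the comparison.** Write F and B for mean follow-up and baseline in arms N and C:

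(F_N − B_N) − (F_C − B_C) = (F_N − F_C) − (B_N − B_C)

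If allocation shifts the baseline difference B_N − B_C by s, the unadjusted comparison of changes moves by −s.

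**5. Illustration of size.** The document gives no SD or correlation for these outcomes, so the following inputs are assumptions: s is in units of the between-person SD, the SD is equal at both times, the baseline/follow-up correlation ρ is 0.5 to 0.8, and there is no true effect. The standardised shift in change is d = s / √(2(1 − ρ)). The rejection probability is that of a two-sided t-test with 2n − 2 degrees of freedom and non-centrality d√(n/2).

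Example with n = 29 and s = 0.2:
- ρ = 0.5: d = 0.2 / 1 = 0.200, non-centrality 0.200 × 3.808 = 0.762, rejection 11.6%.
- ρ = 0.8: d = 0.2 / 0.632 = 0.316, non-centrality 1.204, rejection 22.0%.

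| Shift s | 29 per arm (ρ 0.5 to 0.8) | 40 per arm (ρ 0.5 to 0.8) |
|---|---|---|
| 0.1 SD | 6.6% to 9.1% | 7.3% to 10.7% |
| 0.2 SD | 11.6% to 22.0% | 14.3% to 28.7% |
| 0.3 SD | 20.2% to 42.7% | 26.3% to 55.4% |

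The nominal level is 5%. The 29 is the stated minimum per arm and the 40 the number to be included per arm.

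**6. Price of leaving the baseline out.** Relative to the change score, the standard error of a comparison of 12-week values is multiplied by 1 / √(2(1 − ρ)): 1.00 at ρ = 0.5 and 1 / 0.632 = 1.58 at ρ = 0.8.

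**The case against.** The article does take precautions: an opaque box, sealed envelopes, guidance on what to open first, and disclosure deferred to a second call. Each participant sees only their own parcel and must know or guess what the other arm gets. A pre-inclusion letter covers the aims and sequence of the study, but its text (File S2) is not shown. This stands against saying that concealment has failed, which a reader might infer. The document shows only that it cannot be relied on.

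Other stronger readings are also unsupported:

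- **That sequence concealment is broken.** Randomisation follows inclusion and visit #1, and access to the sequence is restricted. Only participant masking during one week is in question.
- **That blinded site staff see the differing packages at the coordinating center.** The text says the box is handed over there, but not by whom or in whose presence.
- **That the bias favours one arm.** Motivation, disappointment and saving effort pull in different directions.

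It is also fair to say that the follow-up week is measured with allocation openly known, and that repairing the baseline does not remove this. That limits the gain, but a doubtful baseline is a separate and avoidable source of error.

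Finally, section 2.8 allows regression adjustment where baselines differ, and under adjustment the shift need not pass through in full. This is not a cure. It is triggered only by a significant difference, and it would condition on a value that allocation may already have affected.

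**Conclusion.** The point holds for the secondary daily-activity, walking-pain and GPS outcomes. Their baselines are recorded after randomisation, and the parcels differ visibly by arm before the week starts, so the legend's assurance does not rest on firm ground. Any resulting shift reaches the unadjusted change comparison in full with its sign reversed. The table above shows that even a modest shift would matter, but it rests on assumed correlations and shifts. Neither the actual size nor the direction can be determined from the document.

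The primary treadmill distance and the visit #1 6 min test have baselines taken before randomisation and are not affected. Nor is the sample size. The point merits a change of procedure and one added analysis, and it does not threaten the primary conclusion.

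**What to change.** 1. **Procedure.** Dispatch or hand over the NMES box and NMES handbook only after the 7-day week, triggered by the disclosure call already scheduled, and do the same at the coordinating center. Cost: one extra parcel per NMES participant (about 40 if applied to all) and a few days' delay to the start of NMES. Recruitment began in September 2019, so this may reach only part of the sample. The date of the change should be recorded because two baseline procedures would then coexist.
2. **Participants already enrolled.** Label the activity, pain and GPS baselines as post-randomisation in the analysis and the report.
3. **Analysis.** Add a sensitivity analysis comparing the 12-week activity and GPS values between arms, neither subtracting nor adjusting for those baselines. It needs no new data. Its cost is precision: a standard error up to 1.58 times that of the change score if the correlation is 0.8, and no loss at 0.5.
4. **Text.** Correct the Figure 1 legend to say that disclosure is planned for the end of the week but that parcel contents differ by arm before then.
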